## 2. Materials and Methods

### 2.1. Study Design

The RemoteVerify (ReVe) study is a multicentre, prospective, observational study that will be conducted at eight university hospitals (St. Vincent’s Hospital, The Catholic University of Korea; Eunpyeong St. Mary’s Hospital, The Catholic University of Korea; Seoul St. Mary’s Hospital, The Catholic University of Korea; Keimyung University Hospital; Kyungpook National University Hospital; Pusan National University Hospital; Yeungnam University Medical Center; Pusan National University Yangsan Hospital) in Korea, targeting 450 patients (each centre will enrol 50 to 70 patients). This sample size was based on the assumption that the 2-year incidence of major adverse cardiac and cerebrovascular events of patients with structural heart diseases is 10% to 15%, with a confidence interval of 95% and a margin of error of 5%. The desired sample size was calculated as 139 to 196 participants per group using G*Power version 3.1.9.7 [16], and similar patients are needed in the two groups that differ in the timing of RM application. Considering an anticipated 10% loss to follow-up during the study period, the total number of participants needed for this study was determined as 442. We rounded this number up to 225 per group. An interim analysis will be conducted using the variables collected by the planned patient enrolment period (24 months). A second interim analysis will be conducted after at least 12 months of follow-up data have been collected. The final analysis will be performed at the study endpoint after all participants have completed the 24-month follow-up. Starting from the interim analysis, subgroup analyses will be conducted based on the type of underlying heart disease (hypertrophic cardiomyopathy/ischaemic cardiomyopathy/dilated cardiomyopathy/others) and the left ventricular ejection fraction (LVEF; <30%, 30–45%, >45%).

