Eligible study participants will need to meet the following criteria: patients (1) aged 20 years or older with (2) an LVEF below 40% or a structural heart disease confirmed via cardiac imaging, (3) an implantable cardioverter–defibrillator (ICD) or a cardiac resynchronisation therapy (CRT) device compatible with Biotronik Ltd. (Berlin, Germany) wireless monitoring devices, and (4) a predicted life expectancy of more than 6 months, (5) capable of understanding and completing the simple consent form, and (6) never having been enrolled in clinical trials that involve RM before. Patients will be informed that if they want to withdraw their consent to this study, they can stop participating in this clinical trial, and their data will be collected until the withdrawal date. Exclusion criteria are as follows: (1) patients with a life expectancy of 6 months or less, (2) patients with cognitive impairment who are unable to understand the information regarding wireless monitoring or who are unable to provide consent, and (3) patients currently participating in another clinical trial that may be affected by the implementation of wireless monitoring. Patients who have previously participated in clinical trials, those who are currently participating in a clinical trial that the investigator judges will not affect or be affected by this trial, and those who are participating in other observational studies are eligible for this study. If the patient wishes to discontinue participation in the study or dies within 6 months of participation (to be noted separately), they will be considered withdrawn from the study.

Informed consent will be obtained from each participant included in the study. Details of the study protocol are available at ClinicalTrials.gov (study ID: NCT05971225). Patient enrolment started in November 2023 at two centres (40 and 10 patients were enrolled in St. Vincent’s Hospital and Eunpyeong St. Mary’s Hospital, respectively, as of 1 August 2024) after Institutional Review Board approval (VC23DIDI0148; approval date: 11 July 2023) and will continue until October 2025. Follow-up data will be acquired for 24 months after enrolment. We plan to collect the final data in December 2027, and the results of the ReVe study will be published in 2028.

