Patients with CIEDs, except those on warfarin or those with other relevant medical issues (followed up on other clinic consultation schedules), are scheduled for routine clinical follow-ups every 3–6 months. Patient satisfaction surveys are scheduled every 6 months to assess changes in satisfaction levels over time and explore varying trends across device types (‘Survey on telehealth patient experience’ by [name], 2023 [15], modified Korean version 1.3; Table 1). The study is summarised in Figure 1, and the process of the study is also available in Supplementary Table S1.

The primary endpoint will be any MACCE after RM (cardiovascular-related death and hospital admissions related to pre-existing cardiovascular disease), defining variables that are predictive of MACCE and unexpected hospital visits during RM. The secondary endpoints will be patient satisfaction with the time, cost, and quality of care after adopting RM (determined via questionnaires on a 6-month basis) and the staffing/time requirements during RM (measured using electronic medical records).

All files and data generated during the study are stored in a safety deposit box or as copied files secured with passwords accessible only to the investigators. Because this study includes personal identifiers and sensitive information, the data will not be openly accessible. Anonymised study data will be made available to researchers upon reasonable request after the study results are published.

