### 2.3. Statistical Analysis

We will compare outcomes before and after RM via paired *t*-tests in the historical group. We will compare the clinical-, RM-, and device-related variables via independent samples *t*-test between the historic and initiating RM groups. Tests for normality will be provided. If data is non-normal, then *t*-tests and means/standard deviations should be avoided, and Mann–Whitney/Wilcoxon and medians/interquartile ranges should be preferred. For the *t*-tests, we will reject the null hypothesis when the two-sided *p*-value is less than 5%. For the analysis of patient baseline data, continuous variables will be presented as means and standard deviations and analysed using *t*-tests or Wilcoxon rank-sum tests. Categorical variables will be presented as frequencies and percentages. For the analysis of satisfaction with the survey, paired *t*-tests (parametric test) or Wilcoxon signed-rank tests (non-parametric test) will be performed. For surveys conducted only after monitoring, ordinal variables will be analysed using the Mann–Whitney U test, and continuous variables will be analysed using chi-square tests. For patients not completing the follow-up, censoring will be based on the last data collected. Cumulative event probabilities will be estimated with adverse health outcomes, such as patient deaths, inpatient admissions, and MACCEs. Hazard ratios and 95% confidence intervals will be generated with Cox proportional hazards models. For subgroup analyses, the interaction term between the prespecified groups, based on the type of underlying heart disease and LVEF, will be evaluated for the primary outcome. Because of the interim analyses, we will adopt the O’Brien–Fleming method for statistical corrections. For all analyses, we will use two statistical software packages: Stata, version 18 (StataCorp LLC, College Station, TX, USA), and R, version 4.05 (R Foundation for Statistical Computing, Vienna, Austria).

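### The censoring rule does not separate death from dropout; if deaths outside the endpoint are censored, the 2-year probabilities of MACCE and admission are modestly overstated (minor)

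*Protocol article*

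**What the plan says.** - **Censoring** (section 2.3, Statistical Analysis): "For patients not completing the follow-up, censoring will be based on the last data collected". This is the only censoring rule in the article, and it does not mention death.
- **Quantities to be estimated** (section 2.3): "Cumulative event probabilities will be estimated with adverse health outcomes, such as patient deaths, inpatient admissions, and MACCEs". No estimator is named.
- **Effect measure** (section 2.3): "Hazard ratios and 95% confidence intervals will be generated with Cox proportional hazards models".
- **Primary endpoint** (section 2.2, Data Collection): "any MACCE after RM (cardiovascular-related death and hospital admissions related to pre-existing cardiovascular disease". Non-cardiovascular death is not a component.
- **Early deaths** (section 2.1, Study Design): a patient who "dies within 6 months of participation (to be noted separately), they will be considered withdrawn from the study". The sentence does not distinguish causes of death.
- **Entry** (section 2.1): "a predicted life expectancy of more than 6 months", with follow-up of 24 months.
- **Precision target** (section 2.1): a 2-year MACCE incidence of 10% to 15%, a 95% confidence interval and a 5-point margin of error, leading to 225 patients per group.

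**The concern.** A patient who dies before 24 months has not completed follow-up, so the censoring rule, read literally, covers that patient. The early-death sentence in section 2.1 points the same way, because it puts some deaths in the same class as withdrawal.

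Censoring suits a patient whose later event is merely unobserved. It does not suit a patient who can no longer have the event. Non-cardiovascular death rules out a later MACCE, and death from any cause rules out a later admission. If these patients are censored, the estimate proceeds as though they kept the same future risk as the survivors, and the cumulative probability comes out too high. The direction is always upwards, and the bias does not shrink as the sample grows.

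At stake is the absolute 2-year MACCE probability, which is the quantity the precision calculation is built on, and the corresponding probability for admissions. The curve for death from any cause has no competing event and is not affected.

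**Working it through.** **Step 1. The plan's own figures.** The single-proportion precision formula is n = 1.96² × p(1 − p) / 0.05².

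- p = 0.10: n = 138.3, rounded up to 139.
- p = 0.15: n = 195.9, rounded up to 196.

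Both match the stated 139 to 196 per group. Allowing for 10% loss, 2 × 196 / 0.9 = 435.6, so 436, against the stated total of 442. That is close, and the gap plays no part here. Competing deaths do not enter this calculation, so the sample size does not depend on the point.

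**Step 2. Inputs for the bias.**

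- 2-year MACCE probability m = 10% to 15% (section 2.1).
- 2-year non-cardiovascular death probability d = 3%, 5% and 10%. This is an **assumption**; the article gives no figure.
- For admissions, m = 30% with 5–10% deaths. Both are **assumptions**.
- Constant hazards over 2 years.

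**Step 3. Formulae.** Let lm = −ln(1 − m)/2 and ld = −ln(1 − d)/2 per year. With competing deaths censored, one minus Kaplan-Meier at 2 years equals m. The probability that the event actually occurs by 2 years is

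CIF = lm/(lm + ld) × [1 − exp(−2(lm + ld))].

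Example, m = 0.15 and d = 0.10:

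- 2·lm = 0.1625, 2·ld = 0.1054, sum 0.2679.
- 1 − exp(−0.2679) = 0.235.
- CIF = (0.1625/0.2679) × 0.235 = 0.1426.
- Overstatement = 0.1500 − 0.1426 = 0.0074, or 0.74 points.

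**Step 4. Results** (overstatement in percentage points).

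| Assumed other-cause deaths | MACCE 10% | MACCE 15% |
|---|---|---|
| 3% | 0.15 | 0.22 |
| 5% | 0.25 | 0.37 |
| 10% | 0.50 | 0.74 |

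For a 30% admission probability, the overstatement is about 0.7 points at 5% deaths and 1.4 at 10%.

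**Step 5. Sensitivity to how the inputs are read.** Suppose instead that the 10–15% is the true cumulative incidence F1, and that the death figure is the proportion F2 dying before any MACCE. Then the total hazard is H = −ln(1 − F1 − F2), the MACCE share is H1 = H × F1/(F1 + F2), and the censored estimate is 1 − exp(−H1). The overstatement is 0.16–0.24 points at 3%, 0.27–0.41 at 5% and 0.56–0.85 at 10%. For a 30% admission incidence it is 0.87 at 5% and 1.83 at 10%. The order of magnitude is the same.

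**Step 6. Scale.** The 95% half-width at 225 per group is 1.96 × √(p(1 − p)/225): 3.92 points at 10% and 4.67 at 15%. At 5% other-cause deaths, the Step 4 bias is 0.25/3.92 = 6% to 0.37/4.67 = 8% of the half-width. At 10% deaths it is 0.50/3.92 = 13% to 0.74/4.67 = 16%.

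**Step 7. Between groups.** If 2% of one group and 8% of the other died of other causes (assumed), with equal true MACCE incidence, the Step 5 formula gives 10.10% versus 10.44% at a true 10%, and 15.16% versus 15.67% at a true 15%. The spurious difference is 0.3 to 0.5 points.

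**The case against.** The strongest objection is that the article never says non-cardiovascular deaths will be censored. The rule speaks of patients who do not complete follow-up. Kaplan-Meier is not named, and cumulative event probabilities could mean cumulative incidence functions. Deaths are themselves listed as an outcome, and section 2.2 plans cardiac mortality as a proportion of overall mortality, so causes of death will be known. A special sentence for deaths within 6 months may imply that later deaths are not withdrawals. The choice of estimator is also something an article commonly leaves to the full protocol or analysis plan.

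Much of this stands. A reader might infer that the plan does censor these deaths and that its MACCE and admission probabilities are therefore overstated. The text does not support that as fact; the overstatement is conditional on applying the rule to deaths. A reader might also infer that the two groups' curves cannot be compared. The article gives no reason to expect different non-cardiovascular mortality, and even a marked assumed imbalance moves the difference by only 0.3–0.5 points. The life-expectancy criterion is an entry minimum and says nothing about how many will die of other causes. The hazard ratios are not in question, because a Cox model that censors competing deaths estimates a cause-specific hazard ratio.

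One part does not stand. This is more than an unnamed estimator. The article fixes a censoring rule with no exception for death. Once a competing death has been coded as censored, naming a better estimator does not help: Aalen-Johansen with no competing event coded reduces to one minus Kaplan-Meier. The rule itself needs the exception.

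**Conclusion.** The point holds as a minor, conditional one. The only censoring rule does not separate death from dropout, and section 2.1 labels early deaths as withdrawals. If deaths outside the endpoint are censored on that basis, the 2-year MACCE probability is overstated by about 0.15–0.4 points at 3–5% non-cardiovascular deaths and by up to about 0.75 points at 10% (0.85 under the alternative reading of the inputs). The overstatement is larger for admissions if they are commoner.

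These sizes rest on constant hazards and on assumed other-cause mortality. They are well inside the plan's own sampling error, and neither the sample size nor the hazard-ratio values change. The figures cover only deaths outside the endpoint. How early cardiovascular deaths are counted is a separate question and is not included.

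**What to change.** In section 2.3, or in the analysis plan it refers to:

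1. Reserve censoring for withdrawal of consent, loss to follow-up and end of follow-up. State that the withdrawal label for early deaths in section 2.1 does not make those deaths censored observations.
2. Name non-cardiovascular death as the competing event for MACCE, and death from any cause as the competing event for inpatient admission.
3. Estimate cumulative incidence with the Aalen-Johansen estimator, with these competing events coded.
4. Label the Cox hazard ratios as cause-specific. Their values do not change.

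The cost is a few sentences of analysis wording. No new data are needed, since cause of death is already required for the primary endpoint, and both planned packages, Stata and R, can do the analysis.

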## 3. Discussion

This study will provide evidence for the development of guidelines and policies for RM of patients suffering from serious cardiac diseases. It may also assist in establishing insurance standards for RM in South Korea. Patients with CIEDs need regular follow-ups for their underlying cardiac conditions, alongside planned check-ups for the implanted devices. Although the use and provision of expensive and precise medical technologies, procedures, and drugs to many people at low prices are desirable, the number of patients is too large compared to that of medical staff who offer such services. Thus, time and physical constraints limit the provision of appropriate services. As physicians have an up-to-date understanding of patient health information before the visit, RM adoption can improve the efficiency of short, in-office consultations, allowing them to provide appropriate services. The perspectives of patients with CIEDs and the physicians may differ, as patients desire adequate attention and care. Therefore, the abovementioned factors may lead to patient and/or physician dissatisfaction and inadequate knowledge of CIED recipients regarding their disease status. This may result in poor patient compliance regarding care and self-administered treatments [17]. The number of CIED recipients is gradually increasing owing to the ageing population, which may exacerbate compliance problems and result in poor clinical outcomes. The need for RM of CIEDs is more important for individualised and optimised patient management than ever. To effectively utilise RM, cooperation from patients and their guardians and a sufficient understanding and education regarding RM and their disease are essential. Patient awareness and collaboration may contribute to their satisfaction and improve clinical outcomes.

The workload of RM-related personnel and establishing adequate fees for their medical services remain unsolved [15,18]. Consensus guidelines are not feasible because of the differences in healthcare systems worldwide [19,20,21,22,23,24,25,26]. In a national insurance system such as that in South Korea, evaluating specialised personnel and adequate monitoring fees is necessary to enable the widespread adoption of RM. As monitoring is crucial for patients with structural heart diseases, we believe that the ReVe study can serve as a basis for preparing the professional manpower needed for RM, provide evidence for the time required for RM, and establish an appropriate medical fee system. Countries with similar healthcare systems can work together toward solutions. However, RM-related personnel education and preparation are crucial to fully utilise RM in medical services. This study is anticipated to assist in establishing guidelines for patients with CIEDs and underlying structural heart diseases who need more dedicated and tailored management. Further, this study will provide sound evidence for developing healthcare policies and determining suitable medical costs and RM-related personnel requirements in South Korea and other countries with similar national health insurance systems. The results of the ReVe study will improve the prognosis and safety of patients with severe heart disease and allow for assessing the resulting demand for specialised personnel and appropriate medical costs (The ReVe study is registered on ClinicalTrials.gov under the study ID NCT05971225).

## Figures and Tables

**Figure 1 jcm-14-01150-f001:**
[figure not shown]
ReVe study protocol.

**Table 1 jcm-14-01150-t001:** Survey on patient satisfaction with remote monitoring (modified Korean version by [name]).

Question	Strongly Agree	Agree	Neutral	Disagree	Strongly Disagree
I experienced much overall discomfort owing to remote monitoring					
2. I feel that my health and the CIED were better cared for with remote monitoring than with conventional in-office visits					
3. Using CardioMessenger was difficult					
4. Using CardioMessenger caused an inconvenience in my daily life					
5. Remote monitoring has helped me manage my health					
6. I am satisfied with the use of remote monitoring					
7. Remote monitoring has advantages in terms of time and cost compared to visiting the hospital					
8. I want to continue remote monitoring					
9. I would like to recommend remote monitoring to other patients with CIEDs					

CIED, cardiac implantable electronic device.

## Data Availability

Data used in this study are and will be available from the corresponding author ([name]) upon reasonable request to bona fide researchers.
